## 5.2 Dose-Limiting Toxicity (DLT)

A DLT is an event, defined below, which, in the opinion of the investigator, is possibly, probably, or definitely attributable to the CAR T cell product and which occurs from the time of initial CAR T cell infusion through 28 days following the final CAR T cell infusion. The Maximum Tolerated Dose Regimen (MTDR) will be established by the occurrence of DLTs which occur from the time of initial CAR T cell infusion through 7 days following the final CAR T cell infusion received during Course 2. See Section 9.9.4 Definition and determination of MTDR and RP2DR, for information on establishing MTDR.

The definition of a DLT includes all  $\geq$  Grade 3 Common Terminology for AEs (CTCAE) v5 toxicities **except**  $\geq$  Grade 3 toxicities that are known to be related to CAR T cells [45], listed below.

Exceptions to  $\geq$  Grade 3 DLTs:

- Grade 3 CRS that decreases to  $\leq$  Grade 2 within 72 hours of onset
- $\geq$  Grade 3 hypotension, fever, chills not controlled with medical intervention that decrease to  $\leq$  Grade 2 within 72 hours
- $\geq$  Grade 3 activated PTT, fibrinogen, and/or INR that are asymptomatic and resolve within 72 hours
- $\geq$  Grade 3 hypoglycemia and/or electrolyte imbalance that are asymptomatic and resolve within 72 hours
- $\geq$  Grade 3 nausea and/or vomiting that decrease to  $\leq$  Grade 2 within 7 days

- Arm A and B only: Grade 3 neurological adverse event that decreases to  $\leq$  Grade 2 within 7 days
- Arm C only: Grade 3 neurological adverse event that decreases to  $\leq$  Grade 2 within 21 days (treatment with dexamethasone and/or bevacizumab is allowed)

The definition of a DLT also includes any related toxicity lasting  $> 14$  days which prohibits the subject from meeting criteria for subsequent CAR T cell infusion.

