### 6.2 Symptoms Associated with CAR T Cell Infusion

Mild, transient symptoms have been observed while receiving or within 24 hours of receiving CAR T cell therapy including fevers, chills, rigors, headache, and, rarely, nausea, vomiting, hypotension, and pulmonary toxicity. Clinical changes may represent a recently reported distinct syndrome, tumor inflammation associated neurotoxicity (TIAN), that consists of immunotherapy-induced fever, headaches, and neurologic changes [84]. The management of these symptoms is outlined below.

*Fever, chills and temperature elevations* > 38.2°C may be managed with additional acetaminophen as clinically indicated, and/or 1 mg/kg meperidine (Demerol) IV for chills (maximum 50 mg). Additional methods such as cooling blankets may be employed for fevers resistant to these measures. All subjects who develop fever and/or chills should have a blood culture drawn and be admitted for IV antibiotics and supportive care.

*Headache* may be managed with additional acetaminophen as clinically indicated, and magnesium, diphenhydramine/metoclopramide, NS fluid, and/or narcotics may be considered.

*Nausea and vomiting* may be treated with additional ondansetron, and diphenhydramine/metoclopramide, scopolamine, lorazepam, and/or olanzapine may be considered.

*Hypotension:*

- Transient hypotension may initially be managed by intravenous fluid administration; however, subjects with persistent hypotension may require transfer to the intensive care unit (ICU) for definitive medical treatment.
- If significant hypotension occurs during the CAR T cell infusion, the infusion should be immediately suspended. Significant hypotension is defined as symptomatic and/or systolic blood pressure < 80 mmHg for age > 12 years, < 70 mm/hg for age < 12 years, or a 15% drop from baseline, whichever value is lower.

- Treatment for significant hypotension will follow institution standard practice.

*Hypoxemia* may be managed by standard clinical practice.

If the CAR T cell infusion is stopped before completion and the symptoms causing cessation return to baseline within 30 minutes, the CAR T cell infusion may be restarted at a slower rate. All product must be infused prior to the expiration time/date listed on the syringe label.

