## **8 REMOVAL FROM PROTOCOL THERAPY & OFF STUDY CRITERIA**

### **8.1 Removal from Protocol Therapy**

A subject may be discontinued from protocol therapy at any time. Subjects will be removed from protocol therapy for the following reasons:

- Subject/family or the investigator feels that it is not in the subject's best interest to continue
- Subject/family is non-compliant with protocol therapy and/or clinic appointments
- Subject receives medical intervention prohibited under this protocol or which will interfere with the ability to assess toxicity or response following CAR T cell infusion
- Subject experiences a DLT following CAR T cell infusion
- Subject does not meet criteria to receive the next CAR T cell infusion as defined in Section 5.5.2
- Subject is pregnant
- Subject meets criteria for removal from study (Section 8.2)

All subjects who discontinue protocol therapy should come in for an End of Therapy/Early Discontinuation Visit per Appendix 2 – Schedule of Procedures and should be encouraged to complete all remaining scheduled visits and procedures.

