### **9.9.2 Dose Regimen (DR) escalation rules**

A subject will be considered DR escalation-evaluable if they are evaluable for MTDR DLT and are counted as part of a 3-subject dose escalation Cohort according to the rules described below.

The following rules will be applied separately and independently for each Arm. DLTs are defined in Section 5.2.

*Dose escalation rules using a modified 3 + 3 design for Arms A, B, and C.* DRs are detailed in Section 5.1.3.

1. Escalation and de-escalation decisions will use cohorts of 3 consecutive toxicity-evaluable subjects treated at the same DR
2. The dose escalation route will be similar to a 3+3 design, and will allow expansion on the tentative MTDR if 1 DLTs out of the first cohort of 3 and 1 DLTs out of the second cohort of 3 were observed
  - a. If 0 DLTs out of the first cohort of 3 (0/3) within a DR, and there is a DR available for escalation, it will escalate to the next DR. If there is no DR

available for escalation, then this DR is considered as tentative MTDR and another cohort of 3 will be treated at the current DR.

- b. If 1 DLTs out of the first cohort of 3 (1/3), a second cohort of 3 will be treated and evaluated at the current DR
  - i. If 0 DLTs out of the second 3 and there is a DR available for escalation, it will escalate to the next DR. If there is no DR available for escalation (1 DLT in first 6), the MTDR will be estimated
  - ii. If 1 DLTs out of the second cohort of 3 (i.e. 2 DLT in the first 6), a third cohort of 3 will be treated at the current DR. If there are 0 DLTs in the third cohort of 3, the MTDR will be estimated. If there is 1 DLT in the third cohort (i.e. 3 DLTs in the first 9), a final cohort of 3 will be treated at the current DR and the MTDR will be estimated once all subjects have been evaluated.
- c. If 2 or more DLTs out of any cohort of 3 ( $\geq 2/3$ ) toxicity-evaluable subjects, the current DR will be shut down and the DR will de-escalate to the previous DR. If the first 2 subjects of any cohort of 3 both experience DLTs and the third subject has not received CAR T cells, stop the cohort at 2 subjects and de-escalate to previous DR and the third subject will become the first subject of a new cohort. If there is no DR available for de-escalation (lowest), the arm will be shut down.

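### Section 5.2's second DLT exception is inverted: read literally, Grade 3 or higher hypotension, fever or chills that treatment controls within 72 hours is a DLT, while an uncontrolled event that recovers as fast is exempt

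*Protocol*

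**What the plan says.** Protocol Section 5.2 defines a DLT as any attributable CTCAE v5 toxicity of Grade 3 or higher, apart from a list of exceptions. Only one item on that list names hypotension, fever or chills. It applies at Grade 3 or above and reads "Grade 3 hypotension, fever, chills not controlled with medical intervention that decrease to" Grade 2 or lower within 72 hours.

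The neighbouring items are built differently:

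- The CRS item, "Grade 3 CRS that decreases to" Grade 2 or lower within 72 hours, has no condition on whether treatment worked.
- The nausea/vomiting item has only a 7-day limit.
- The neurologic items have only a limit of 7 days (Arms A and B) or 21 days (Arm C). The Arm C item adds that "treatment with dexamethasone and/or bevacizumab is allowed".
- The coagulation and electrolyte items add that the event be asymptomatic, but say nothing about control by treatment.

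Section 6.2 expects these symptoms to be treated. Fever and chills "may be managed with additional acetaminophen as clinically indicated, and/or 1 mg/kg meperidine (Demerol) IV for chills", and transient hypotension is first managed with intravenous fluid.

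Section 8.1 lists, as a reason for removal from protocol therapy, "Subject experiences a DLT following CAR T cell infusion". Sections 9.9.2 and 9.10 use DLT counts to run escalation and to halt the expansion cohort.

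**The concern.** An exception should spare the event that is less worrying. As worded, this one spares the event that treatment failed to control and leaves out the same event, recovering equally fast, that treatment did control. Since Section 6.2 makes treatment the ordinary course, the omitted case is the ordinary one.

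The DLT definition drives a primary objective (the maximum tolerated regimen) and decisions are taken on cohorts of three. One event classified by the letter of the text instead of its evident purpose can therefore change the next step, and it ends that subject's treatment.

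**Working it through.** The plan states no figure for this rule, so the check is of logic, followed by the consequences that the protocol's own rules attach to one extra DLT.

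**Step 1. The exception as a truth table.** The event is attributed to the CAR T cells, is Grade 3 or higher by CTCAE, is one of the three named terms, and is not exempt under the CRS item.

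| Controlled by treatment? | Grade 2 or lower within 72 h? | As written | Qualifier deleted | Qualifier changed to require control |
|---|---|---|---|---|
| No | No | DLT | DLT | DLT |
| No | Yes | Exempt | Exempt | DLT |
| Yes | No | DLT | DLT | DLT |
| Yes | Yes | **DLT** | Exempt | Exempt |

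The last row is the defect. Deleting the qualifier changes that row only. Changing it to require control changes two rows, because the uncontrolled but fast event then becomes a DLT.

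**Step 2. Which terms the qualifier covers.** It follows a comma list ending in chills and may attach to all three terms or to chills only. If only to chills, fever and hypotension are exempt on recovery alone and the table applies to chills. The text does not settle this.

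**Step 3. How many events can be affected.** Section 11.5 grades CRS on its own scale, driven by hypotension and hypoxia. Hypotension responsive to fluids is Grade 2 CRS. Hypotension on one vasopressor is Grade 3 CRS, which is exempt if it recovers in 72 hours. Much CAR T-related fever with hypotension therefore never reaches the second exception. What clearly remains is chills, and hypotension outside CRS. Note 2 to Section 11.5 also allows CTCAE grading of organ toxicities associated with CRS. That Section 5.2 lists these three terms separately from CRS suggests that some such events were expected. No rate is given, and Section 6.2 describes infusion symptoms as mild and transient, with hypotension rare. I assume no rate.

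**Step 4. What one such DLT does.** These steps hold for any single extra DLT and are not a measure of this bullet.

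- First cohort, no other DLT: 0/3 (escalate) becomes 1/3 (three more subjects at the same regimen).
- First cohort, one other DLT: 1/3 (three more subjects) becomes 2/3. The rule "If 2 or more DLTs out of any cohort of 3" then closes the regimen; at DR 1 the arm is shut down.
- Second cohort with no other DLT, after 1/3: 1/6 = 16.7% becomes 2/6 = 33.3%. At 1/6, "If 0 DLTs out of the second 3 and there is a DR available for escalation, it will escalate to the next DR". At 2/6 a third cohort is treated, and "If there are 0 DLTs in the third cohort of 3, the MTDR will be estimated", so escalation does not follow.
- Expansion, 7 to 9 subjects at the chosen regimen: 2 DLTs (2/9 = 22.2% to 2/7 = 28.6%) becomes 3 (3/9 = 33.3% to 3/7 = 42.9%). Section 9.10 gives 3 among 7 to 9 as an example that halts infusions for DSMB review.

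**The case against.** The best reply is that the intent is plain. The phrase can be read as an outer limit: even an event that resists treatment is exempt if it recovers in 72 hours, so the milder, controlled event is exempt all the more. The suspension rule in Section 9.9.3 exempts Grade 4 fever with no control condition, which fits that reading. The weekly safety group in Section 9.11.1 reviews DLTs and could apply it. The phrase may also restate a CTCAE grade criterion for chills. If it does, and attaches to chills only, there would be no controlled Grade 3 chills event to misclassify.

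These readings are plausible, but the protocol states none of them. The exceptions form a closed list, nothing tells the safety group to look past the words, and the CTCAE criteria are not reproduced, so the last possibility cannot be checked here. The reply lowers the likely harm without making the text correct.

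The objection that few events are affected stands, as Step 3 shows.

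A reader might extend the list in Step 4 to a third cohort, where 2/9 becomes 3/9 and a final three subjects are treated. That step is not settled. Section 9.9.1 bars assigning new subjects to a regimen once its DLTs exceed two, which conflicts with the final cohort in Section 9.9.2. I do not rely on it.

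A reader might also infer that the definition is too lenient, because this bullet covers Grade 3 and above and so takes in Grade 4 hypotension, while the CRS item stops at Grade 3. That is a separate clinical choice running in the opposite direction. The text does not show it to be a mistake, and the exceptions to the Section 9.9.3 rule do not name hypotension.

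**Conclusion.** The point holds in a limited form. Followed literally, Section 5.2 classifies a controlled, fast-recovering hypotension, fever or chills event of Grade 3 or higher as a DLT and exempts its uncontrolled counterpart. This rests on reading the bullet as two joint conditions within a closed list, and it applies only to attributed, CTCAE-graded events outside the exempt CRS category. Under the chills-only reading it shrinks to chills.

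Its size cannot be put as a probability. Per event, the cost is one subject removed from therapy and possibly one changed cohort or expansion decision.

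Two stronger conclusions are tempting, and the documents support neither. The first is that DLT counts or regimen decisions already taken are wrong: the protocol reports no adjudicated event, so no misclassification is shown. The second is that the inversion could let an unsafe regimen through: the faulty row adds DLTs, so the error is conservative for dose selection. The correction should be made because the rule as stated gives a wrong result and costs almost nothing to put right.

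**What to change.** Delete the five-word control qualifier that follows chills in the second exception of Section 5.2. Recovery to Grade 2 or lower within 72 hours is then the sole test for all three terms, in line with the CRS, nausea/vomiting and neurologic items. This also removes the doubt over which terms the qualifier covers.

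Do not simply drop the negation so that control is required, unless the sponsor wants uncontrolled events that recover within 72 hours, now exempt, to become DLTs.

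Then check any already adjudicated related Grade 3 or higher hypotension, fever or chills events against the corrected wording, and restate DLT counts only if a classification changes.

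The cost is a one-bullet amendment and a short review of existing records, with no new data or subjects.

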### **5.3 Apheresis for T Cell Isolation**

Subjects who do not already have an apheresis product available for use in manufacturing will undergo apheresis to obtain T cells from which individualized CAR T cell therapy will be manufactured. Apheresis may take place in either an outpatient or inpatient setting and will be performed per institutional standard operating procedure. After meeting requirements for apheresis, subjects will undergo apheresis with a target total lymphocyte collection of  $1 \times 10^9$ .

In instances of manufacturing failure or insufficient availability of starting material subjects may undergo a repeat apheresis procedure if the Principal Investigator feels it may yield a successful product. Subjects who have already initiated CAR T cell infusions and are eligible for ongoing CAR T cell therapy but no longer have available CAR T cell product and who do not have sufficient starting material for additional manufacture may undergo repeat apheresis. All subjects undergoing apheresis or repeat apheresis must meet requirements for apheresis, noted in Section 5.3.1.

#### **5.3.1 Requirements for apheresis**

Subjects with active, severe, infection may not undergo apheresis. For the purpose of this trial, active, severe infection is defined as:

- Positive blood culture within 48 hours of blood draw, OR
- Fever  $> 38.2^{\circ}\text{C}$  AND clinical signs of infection within 48 hours of blood draw

### **5.4 Bridging Therapy**

During the period between apheresis and CAR T cell infusion, subjects may return to the care of their primary physician. Additional therapy aimed at controlling disease burden to allow the subject to meet criteria for CAR T cell infusion may be given. Refer to Section 5.5.1 Requirements for initial CAR T cell infusion and Table 5-2 for Pre-T Cell Therapy Wash-Out Requirements.

### **5.5 CAR T Cell Product Infusion**

#### **5.5.1 Requirements for initial CAR T cell infusion**

The following criteria must be met prior to administration of initial CAR T cell product:

- First 3 subjects (this requirement has been met as of 8/27/2020):

- Age  $\geq 15$  and  $\leq 26$  years
  - Only treated on Arm A or Arm B
- Subjects subsequent to the first 3 treated:
  - Age  $\geq 1$  and  $\leq 26$  years
  - May be enrolled on any Arm (Note: See Section 9.9.1 Arms and DLT observation periods: Subjects may be enrolled on Arm C once 3 subjects have been treated on Arm A and/or Arm B, and at least 1 subject on Arm A or B completes Course 2 without experiencing a DLT. This requirement has been met as of 04/29/20.)
- Subject has a CNS reservoir catheter in place
- Subject is  $\geq 5$  days from CNS surgery, including catheter placement
- Subject has confirmed evidence of persistent, evaluable disease
- Subject is not breastfeeding
- Female subjects of childbearing potential only: subject has a negative pregnancy test within 2 days prior to initial CAR T cell infusion
- Regarding bridging therapy:
  - If the subject has achieved defined partial or complete remission with bridging therapy, the Study Chair or designee will recommend to the subject's treating oncologist that the bridging therapy be continued. The subject may be re-evaluated and would be eligible to receive CAR T cell treatment upon meeting requirements for CAR T cell infusion.
  - The following treatments must be discontinued for the specified duration (washout period) prior to infusion of the CAR T cell product, and subject must have recovered from acute therapy associated toxicities.

**Table 5-2 Pre-T Cell Therapy Washout Requirements**

| Treatment                                                                                                                                                     | Wash-out Period
(prior to CAR T cell product infusion) |
|----------------------------------------------------------------------------------------------------------------------------------------------------------------------|------------------------------------------------------------------|
| Radiation therapy                                                                                                                                                    | ≥ 6 weeks                                                        |
| Bevacizumab                                                                                                                                                          | ≥ 28 days                                                        |
| Cytotoxic chemotherapy                                                                                                                                               | ≥ 21 days                                                        |
| Biologic agents                                                                                                                                                      | ≥ 7 days                                                         |
| Antibody therapy
(eg, murine, chimeric or
humanized monoclonal
antibodies)
T cell growth factors
(eg, IL-2, IL-7 or IL-15)
Interferons
Vaccines | ≥ 3 half-life or 30 days
(whichever is shorter)               |
| Cellular therapy                                                                                                                                                     | ≥ 30 days since last infusion                                    |
| Any investigational agent                                                                                                                                            | ≥ 3 half-life or 30 days
(whichever is shorter)               |

- If the subject is receiving corticosteroids for symptomatic relief from their CNS disease, steroid dosing must be stable or decreasing for ≥ 1 week with a maximum dexamethasone dose of 2.5 mg/m^2/day on the day of the infusion. Corticosteroid physiologic replacement therapy for management of pituitary/adrenal axis insufficiency and/or topical administration (e.g., inhaled or dermatologic) is allowed.
- Subject must have adequate organ function as indicated by:
  - Renal: Serum creatinine ≤ ULN per Table 3-2 Screening Serum Creatinine Values
  - Hepatic: Total bilirubin < 3 times ULN for age OR conjugated bilirubin < 2 mg/dL
  - Respiratory: Oxygen saturation ≥ 90% on room air without supplemental oxygen or mechanical ventilation, and no dyspnea at rest
  - Hematologic: Platelets ≥ 100,000/μL (transfusion(s) allowed to meet criteria)
- No evidence of clinically significant progressive encephalopathy or uncontrolled seizure activity.
- Subject is taking an anti-seizure medication.
- No evidence of active severe infection, defined as: 1) positive blood culture within 48 hours of CAR T cell infusion; or 2) fever > 38.2°C AND clinical evidence of infection within 48 hours of CAR T cell infusion

### **5.5.2 Requirements for subsequent CAR T cell infusion and dose modification**

The following criteria must be met prior to administration of subsequent CAR T cell product:

- No DLT (Section 5.2) has occurred following infusion of CAR T cell (See Section 8 Removal from Protocol Therapy & Off Study Criteria).
- Cryopreserved CAR T cells are available and released for infusion
- Subject must have adequate organ function as indicated by:
  - Renal: Serum creatinine  $\leq$  ULN per Table 3-2
  - Hepatic: Total bilirubin  $< 3$  times ULN for age OR conjugated bilirubin  $< 2$  mg/dL
  - Respiratory: Oxygen saturation  $\geq 90\%$  on room air without supplemental oxygen or mechanical ventilation, and no dyspnea at rest
  - Hematologic: Platelets  $\geq 100,000/\mu\text{L}$  (transfusion(s) allowed to meet criteria)
- No evidence of clinically significant progressive encephalopathy or uncontrolled seizure activity
- Subject is taking an anti-seizure medication
- No evidence of active severe infection, defined as: 1) positive blood culture within 48 hours of CAR T cell infusion; or 2) fever  $> 38.2^{\circ}\text{C}$  AND clinical evidence of infection within 48 hours of CAR T cell infusion
- Subject has a CNS reservoir catheter in place
- Subject is not breastfeeding
- Female subjects of childbearing potential only: subject has a negative pregnancy test within 2 days prior to Week 1 CAR T cell infusion of each Course

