### 5.1.6 Treatment Plan Delays

During each Course, the time interval between each CAR T cell infusion will be according to the Schedule of Procedures and based upon the date of the most recent CAR T cell infusion. The end date of each Course will be the date of completion of Week 4 evaluations per the Schedule of Procedures. The start date of each Course will be the date that the Week 1 CAR T cell infusion required evaluations are performed.

Within Course 1 and 2, if a subject does not meet the criteria to receive a CAR T cell infusion ([Section 5.5.2](#)) on the planned infusion day of a Course regardless of attribution to the CAR T cells, the infusion may be delayed no more than 3 weeks from the planned infusion date. If delayed greater than 3 weeks from the planned infusion date, the subject will be removed from

protocol therapy and will not receive further CAR T cell treatment. See [Section 8.1](#) Removal from Protocol Therapy.

Between Course 2 and Course 3, delays due to family/subject preference, investigator discretion, or due to subject recovery from a surgical procedure (e.g., tumor biopsy) are allowed. Following Course 3, only delays due to subject recovery from a surgical procedure (e.g., tumor biopsy) or due to travel disruptions are allowed. During the delay subjects must continue to be followed for concomitant medications (Section 7.8) and adverse events (Section 7.9). Criteria for removal from protocol therapy in Sections 5.5.2 and 8.1 will override family/subject/investigator preference delays as noted above.

Beyond Course 2, subjects must receive at least the Week 1 infusion of any Course but may skip the other scheduled infusions. If a subject does not receive an infusion within 3 weeks of the Week 1 infusion, the next infusion will be considered a new Course. If infusions are delayed, the subsequent pre- and post-visit evaluations/procedures (see [Appendix 2 – Schedule of Procedures](#)) will be timed based upon the next administered CAR T cell infusion. If an infusion is not given, the pre- and post-visit procedures for that infusion are not required. If delay to subsequent infusion is greater than 8 weeks from prior infusion, disease response assessment must be obtained prior to dosing.

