### **7.18.1 Disease response assessment during active treatment**

Disease Response will be assessed within 1 week following the last CAR T cell infusion on even courses (e.g., 2, 4...) but may be delayed up to 4 weeks due to clinical or scheduling issues. This evaluation must be performed prior to receiving Week 1 CAR T cell infusion on the subsequent odd course (e.g., 3, 5...).

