#### **10.1.4 Response criteria for target lesions**

*Complete Response (CR)*: Disappearance of all target lesions

*Partial Response (PR)*:  $\geq 50\%$  decrease in the sum of the products of the two perpendicular diameters of all target lesions (taking as reference the initial baseline measurements)

*Stable Disease (SD)*: Neither sufficient decrease in the sum of all target lesions to qualify for PR, nor sufficient increase to qualify for progressive disease

*Progressive Disease (PD)*:  $\geq 25\%$  increase in the sum of the products of the perpendicular diameters of the target lesions (taking as reference the smallest sum of the products observed since the start of treatment)

*Immune-Related Progressive Disease (irPD)* may occur in the setting of CAR T cell therapy and can manifest as increased disease and/or new lesions and is distinct from PD [93]. irPD will be documented as SD. irPD must occur within 6 months of the initiation of immunotherapy, cannot last longer than 6 months, and cannot correspond to neurologic decline that is definitely attributable to worsening disease. If irPD is suspected:

- Re-imaging is recommended in 3 months and if progressive disease is confirmed, subject will be determined to have PD
- Biopsy should be considered and if pathology is consistent with progressive disease, subject will be determined to have PD

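### The 5-day interval after CNS surgery guards only the first infusion; the Section 5.5.2 checklist for later infusions sets no minimum

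*Protocol*

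**What the plan says.** Two checklists decide whether cells may be given. Section 5.5.1 applies to the initial product only and requires that the subject be at least 5 "days from CNS surgery, including catheter placement". Section 5.5.2 applies from the second infusion on and begins "The following criteria must be met prior to administration of subsequent CAR T cell product". It repeats the organ function, encephalopathy and seizure, anti-seizure medication, infection, breastfeeding and pregnancy items. Its only item touching surgery is "Subject has a CNS reservoir catheter in place". It does not refer back to 5.5.1.

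Surgery during treatment is foreseen. For the gap between Courses 2 and 3, Section 5.1.6 states that "delays due to family/subject preference, investigator discretion, or due to subject recovery from a surgical procedure (e.g., tumor biopsy) are allowed". For later treatment it states "Following Course 3, only delays due to subject recovery from a surgical procedure (e.g., tumor biopsy) or due to travel disruptions are allowed". Within Courses 1 and 2, the ground for delay is failure to meet the 5.5.2 criteria, with a ceiling: "If delayed greater than 3 weeks from the planned infusion date, the subject will be removed from" protocol therapy.

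The response sections prompt biopsy. For suspected immune-related progression, which is recorded as stable disease, Section 10.1.4 reads "Biopsy should be considered and if pathology is consistent with progressive disease", the subject is then classed as progressive. Section 10.1.6 recommends biopsy of a residual lesion when a complete response depends on it. The assessment that leads to such a biopsy sits just ahead of further dosing; Section 7.18.1 says "This evaluation must be performed prior to receiving Week 1 CAR T cell infusion on the subsequent odd course".

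**The concern.** The sponsor judged that an operated site needs at least 5 days before cells and a saline flush are pushed through a catheter into the tumor cavity or ventricle. Nothing in the text at hand explains why that need should lapse after the first infusion. The protocol itself suggests biopsies in children who may stay on treatment, at a point in the schedule close to the next dose.

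The main stake is the safety of the child. There is also a smaller effect on the data. Under Section 5.2 an event that is only possibly attributable to the product can be a DLT. A surgical complication shortly before or after an infusion is hard to attribute, and Appendix 4 puts intracerebral hemorrhage at Grade 4. In Courses 1 and 2, one such event counted as a DLT turns 0/3 into 1/3 and, under Section 9.9.2, calls for a second cohort of 3 at that dose regimen.

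**Working it through.** The plan states no figure for this point, so there is none to reproduce. The check is a comparison of texts, followed by simple date arithmetic on what the fix would cost.

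**Is there a minimum interval from surgery anywhere for later infusions?**

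- Section 5.5.1: 5 days, initial infusion only.
- Section 5.5.2: none.
- Section 5.1.6: delay for surgical recovery is allowed after Course 2, with no minimum and no duty to delay. In Courses 1 and 2 the stated trigger is an unmet 5.5.2 criterion, and recent surgery is not one.
- Appendix 2, footnote g to Tables 1a and 1b: at least 7 days, counted from the previous infusion and not from surgery.
- Sections 5.6 and 8.1: no interval.

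Minimum from surgery: 5 days for infusion 1, none stated afterwards.

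**Which infusions does this cover?** Arms A and B plan 3 infusions per course and Arm C plans 2 (Section 5.1.1).

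- Arms A and B, Courses 1 and 2: 2 × 3 = 6 infusions, of which 6 − 1 = 5 fall under 5.5.2.
- Arm C, Courses 1 and 2: 2 × 2 = 4 infusions, of which 4 − 1 = 3 fall under 5.5.2.
- Course 3 onward: all.

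**What wait would a 5-day rule add between courses?** The Week 3 infusion and the next Week 1 infusion are 14 days apart (Week 3, rest in Week 4, then Week 1). With surgery k days after the Week 3 infusion, the added wait is max(0, k + 5 − 14).

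- k = 9: 9 + 5 − 14 = 0 days
- k = 10: 1 day
- k = 14: 5 days

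So surgery up to day 9 adds nothing, and surgery on days 10 to 14 adds 1 to 5 days.

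**Could the rule collide with the 3-week limit in Courses 1 and 2?** Only if surgery comes late in a delay that is already running. With surgery d days after the planned infusion date, the earliest infusion is day d + 5, against a limit of 21.

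- d = 16: day 21, allowed
- d = 17: day 22, 1 day over
- d = 21: day 26, 5 days over

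Surgery up to day 16 of the delay fits. Surgery on days 17 to 21 would lead to removal under the existing limit.

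**The case against.** The strongest reply is that the protocol already handles on-treatment surgery, through clinical recovery and not a fixed number. Section 5.1.6 names surgical recovery twice, and a recovery-based rule may exceed 5 days after a larger operation. Enrollment is at one hospital (Section 9.1). Institutional infusion guidelines apply (Section 5.6), safety is reviewed weekly while subjects are active (Section 9.11.1), and the investigator may stop therapy in the subject's interest (Section 8.1). Infection, seizure, encephalopathy and platelet checks precede every infusion. All of this stands and reduces the risk. It does not supply a mandatory minimum, and for Courses 1 and 2 the delay rule gives no express surgical ground.

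A second reply is that 5.5.2 is deliberately shorter: it also omits the washouts, the steroid cap and the evaluable-disease item. That is true, but several of those omissions have a visible reason. Section 5.7.4 bars anti-tumor chemotherapy, other immunotherapy and other investigational agents during treatment and exempts corticosteroids, and Section 6 uses steroids to manage toxicity. No comparable reason is given for dropping the surgical interval.

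A third reply is that on-treatment catheter replacement is nowhere described. That is correct. It is an inference from 5.5.1 counting placement as CNS surgery and from 5.5.2 requiring a catheter in place. Tumor biopsy is the case that the document names, and the point rests on it. The background section on CNS catheters (1.10) is not in the text at hand and may say more.

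A reader might infer that the protocol directs or endorses infusion straight after surgery. It does not: delay is permitted and clinical judgment applies. The defect is a missing floor.

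**Conclusion.** The point holds as an inconsistency between two mandatory checklists: a 5-day safeguard covers the first infusion and is absent for every later one, while the protocol foresees on-treatment biopsy and makes a recovery delay optional. It is a cheap improvement for patient safety that the sponsor could make. No sample size, escalation rule, DLT definition or stated probability is affected.

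The practical size is unknown. A reader might be tempted to put a number on the children at risk by applying a guessed surgery rate to the 90 planned subjects. The documents do not support this. They give no rate of on-treatment surgery, and such a figure would count operations, whereas the relevant group is those infused within 5 days of one. Surgery up to day 9 after a Week 3 infusion already clears 5 days on the normal schedule, so the relevant group is smaller and could be close to zero.

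The conclusion assumes that the sections not shown, 1.10 in particular, do not impose the interval on later infusions. Even if they mention one, 5.5.2 is the list that must be satisfied before each later dose, so the line belongs there.

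**What to change.** Add to Section 5.5.2: *At least 5 days have passed since any CNS surgery, including placement or revision of a catheter.*

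Add to Section 5.1.6: *Waiting for this interval is a permitted delay in any Course, within the existing 3-week limit in Courses 1 and 2, and is not in itself a reason for removal under Section 8.1.* The clarification is needed because Section 8.1 lists an unmet 5.5.2 criterion as a reason for removal, so the new line alone could be read as ending therapy for a child who only needs to wait.

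The cost is a wait of up to 5 days after surgery and, rarely, a removal when surgery falls on days 17 to 21 of an already delayed infusion in Courses 1 or 2. Lengthening the 3-week limit to avoid that rare case is not warranted: Section 5.1.6 already lets an unmet 5.5.2 criterion delay an infusion by up to 3 weeks. The DLT window for the MTDR ends 7 days after the final Course 2 infusion, so it moves with any delay and needs no change. No new data are collected.
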